### Participants’ eligibility

The study participants are women of child bearing age who are eligible for cervical cancer screening according to the Ethiopian national cervical cancer prevention and control guideline [14]. Accordingly women aged 30–49 years are targets for cervical cancer screening program and our research will be carried out within this program framework. Women will also satisfy the requirements of legal residency within their respective living quarters for at least six months, have not had received the screening services within the last 5 years, non-pregnant, beyond three months of postpartum, have not had hysterectomy, have not been diagnosed for any gynecological cancer including cervical cancer. These eligible women will be identified through censusing or health post records.

### Recruitment of participants

The Kembata Tembaro and Hadiya zones where the study districts have been situated belong to administrative structures in the Southern Nations, Nationalities and People Regional State of Ethiopia. These two zones were among the low performing zones as identified by the regional health bureau regarding utilization of cervical cancer screening services in 2021. This scenario drew the attention of the researchers to conduct this trial in these settings. Initially two districts, one from each, will be identified from the two zones for this study based on the availability of cervical cancer screening services. Then, sixteen geographically non-adjacent clusters or kebeles will be identified from the existing kebeles within the two study districts.

First, all possible non adjacent kebeles within each district will be listed. Then, among all non-adjacent kebeles, those which are relatively far apart to each other will be selected and included in the study. Therefore, non-adjacency and greater distance between kebeles will be the two selection criteria. Even though, it is difficult to indicate the distance in figures between included kebeles, we will leave at least one kebele between kebeles included for our research which may serve as buffer area between them. All the study clusters are kebeles located in the rural areas of the districts with the average population size of five thousand.

We will randomly assign the selected clusters in to intervention and control groups using block randomization technique as indicated in details below. We will conduct a census and/or use health post records to identify all the eligible women for cervical pre-cancer screening in the selected clusters. Subsequently, sampling frame will be created. Then, we will employ simple random sampling technique to select study participants from each cluster for each arm. Equal number of participants will be selected from each cluster.

Those women who consent to participate in the study will be included and requested to sign an informed consent to ensure voluntary participation. Selected women at each arm will be reached by health extension workers and the data collectors at their home. Once consent is obtained, each participant will be interviewed to complete a baseline survey. The baseline questionnaire includes items on cervical cancer screening knowledge, attitudes, screening experiences, and socio-demographic variables. Similarly end line survey will be conducted at six months.

### Randomization

The clusters or kebeles are the units of randomization in our study. Initially, eight non-adjacent clusters from each district will be identified from the two districts. Before randomization, we will stratify the clusters by the study districts and create separate list of clusters alphabetically for each district. The stratification will be done to evenly distribute any known and unknown district level confounders across the study arms. Each cluster will be assigned a unique cluster code. Then, the statistician will assign the eight clusters in to two blocks of size 4 according to the order they appeared alphabetically. The statistician will randomly select the randomization sequence of clusters for each block using the sealed lots of the six possible permutations within the block.

The clusters in each block will be randomly assigned to intervention and control arms according to the randomization sequence evident by the selected permutation within in the block for the stratum. We will repeat the same process for blocks of clusters in the other stratum. Consequently, four clusters will be obtained from each district which will form eight clusters to the intervention arm and eight clusters to the control arm maintaining 1:1 random allocation ratio. Both the stratification and randomization techniques will help actual and potential confounding factors distribute evenly across the study arms which will eventually ensure comparability of the arms.

The statistician will be made unaware of the actual study arms to mask the knowledge about which group will receive the intervention and which group will receive the usual care. This will be achieved by representing the study arms and clusters by confidential codes. Health extension workers will carry out identification of eligible participants’ for the study and subsequent intervention administration activities. Assessors will also be made blind to the nature of clusters with respect to intervention administration.

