**Methods:**

In this interventional study we will randomly assign 16 clusters (kebeles) in to the intervention and the control arm using block randomization. The study will employ a cluster randomized controlled trial. Women are eligible to participate in this study when they satisfy certain eligibility criteria; being in the age range of 30–49 years, no history of hysterectomy, did not receive cervical cancer or pre-cancer treatment and non-pregnant. Home based couple education and counseling will be provided to the eligible participants within the intervention group, while the control group receives standard of care. Base line and end line surveys will be completed by interviewing 288 eligible women to evaluate the effect of couple education and counseling on the knowledge, attitude and cervical cancer screening uptake. Generally the intervention lasts for six months. The results of baseline & end line surveys will be compared between the groups to determine the effectiveness of the intervention. Blinding is not possible due to the clustering of the trial arms.

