### Study setting

The geographic location for our study is Kembata Tembaro and Hadiya zones which are located in the Southern Nations Nationalities and Peoples’ Regional State. The total number of age eligible women (30–49 years) for cervical cancer screening in the study zones constitutes 19.2% of women of reproductive age group residing in the zones. Kembata Tembaro zone comprises 8 districts and 3 city administrations with the total number of 150 clusters or kebeles, the smallest administrative units, of which 9 are located in the city administrations. The zone has one general hospital, four primary hospitals, 33 health centers and 138 health posts. Hadiya zone is administratively organized in to 13 districts and 4 city administrations having a total number of 329 clusters. The zone has one comprehensive specialized hospital, three primary hospitals, 61 health centers and 317 health posts.

The health care of women of child bearing age in general and maternal & child health care services in particular are of the main strategic pillars of the health service delivery efforts in the zones. Cervical cancer prevention and control activities are being integrated in to the routine health care delivery as an important health service package for the women’s health. Currently, cervical cancer screening services are being implemented at selected hospitals and health centers of the zones where our research activities will base these facilities.

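### Forming the randomisation blocks alphabetically adds no balance beyond district; ordering kebeles by access to screening would reduce chance imbalance at almost no cost

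*Protocol article*

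**What the plan says.** The Abstract (Methods) states that the trial will "randomly assign 16 clusters (kebeles) in to the intervention and the control arm using block randomization". The Randomization section gives the steps. Eight non-adjacent kebeles are taken from each of two districts, and district is the stratum: "The stratification will be done to evenly distribute any known and unknown district level confounders across the study arms". Within each district the kebeles are listed by name, and "the statistician will assign the eight clusters in to two blocks of size 4 according to the order they appeared alphabetically". For each block one sequence is drawn from "sealed lots of the six possible permutations within the block", giving four kebeles per arm in each district and eight per arm overall, "maintaining 1:1 random allocation ratio". The section closes by saying that stratification and randomisation together will help "confounding factors distribute evenly across the study arms which will eventually ensure comparability of the arms".

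Two other sections bear on the choice. Study setting says that "cervical cancer screening services are being implemented at selected hospitals and health centers of the zones". Recruitment of participants says that, among the non-adjacent kebeles, "those which are relatively far apart to each other will be selected and included in the study", and that all study kebeles are rural. No distance or travel time from any kebele to a screening facility is given.

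**The concern.** All sixteen kebeles are known before allocation, so the blocks are not needed to keep the arms level during sequential enrolment. They can do two things: force equal numbers, and balance whatever factor orders the list. Equal numbers per district would also follow from one draw of four out of eight. The ordering factor is the name of the kebele, which there is no reason to link to screening uptake.

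The primary outcome is completion of a test that requires a visit to a facility. Ease of reaching that facility is therefore a natural kebele-level influence on uptake, and the setting makes it plausible that it varies. With eight kebeles per arm, one arm can by chance receive more of the easily served kebeles, which shifts the uptake difference up or down for reasons unrelated to the intervention. The scheme has a blocking step that could limit this and does not use it.

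The planned difference of differences (Primary outcome) would not remove such a gap. Women screened in the last five years are ineligible (Participants' eligibility), and the baseline proportion covers that same window (Statistical analysis). Baseline uptake is thus zero by design in both arms, and the contrast reduces to the end-line difference.

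**Working it through.** **Inputs from the protocol.** 16 kebeles, 8 per district, 2 blocks of 4 per district, 6 permutations per block (Randomization); 18 women per kebele, so 8 × 18 = 144 per arm (Sampling procedure); uptake 15.5% and 35.5%, design effect 2 (Sample size).

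**Assumptions, not in the protocol.** Kebeles are evenly spaced in access, ranks 1 to 8 in each district. Alphabetical order is unrelated to that rank. Uptake falls linearly by a total of 10, 15 or 20 points from rank 1 to rank 8, that is 10/7, 15/7 or 20/7 points per rank.

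**Step 1: the plan's own figure.** The point disputes no figure, but the sample size can be reproduced. A one-sided 5% test with 80% power and continuity correction needs 68 per arm. Then 136 × 2 = 272, and 272 × 1.05 = 285.6, which rounds up to 16 × 18 = 288. This total is unaffected.

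**Step 2: alphabetical blocks, one district.** If names are unrelated to access, every 4-versus-4 split is equally likely. Over all 70 splits, the difference between arms in mean rank has SD 1.732.

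**Step 3: blocks ordered by access, one district.** With blocks {1–4} and {5–8} there are 6 × 6 = 36 allocations, and the SD is 0.913. The variance ratio is 0.278, a reduction of 72%.

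**Step 4: both districts.** Averaging two independent districts divides the SD by √2: 1.732/√2 = 1.22 ranks against 0.913/√2 = 0.65 ranks.

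**Step 5: convert to uptake.** Multiply by points per rank. The probabilities come from enumerating the two-district allocations exactly (70 × 70 = 4,900 and 36 × 36 = 1,296).

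| Assumed gradient | SD, alphabetical | SD, by distance | Gap ≥ 5 points, alphabetical | Gap ≥ 5 points, by distance |
|---|---|---|---|---|
| 10 points | 1.7 | 0.9 | 0.3% | 0% |
| 15 points | 2.6 | 1.4 | 5.0% | 0% |
| 20 points | 3.5 | 1.8 | 18.9% | 0.8% |

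**Step 6: does the result need a linear gradient?** Suppose instead that k of the 8 kebeles in each district have good access. With k = 2, the arms differ by 0, 2 or 4 such kebeles with probability 0.42, 0.49 and 0.09, whether the blocks are alphabetical or absent. The same agreement holds for k = 3 and 4 within simulation error. Blocks ordered by access lower the chance of a difference of 4 or more from 9.1% to 5.6% (k = 2), from 13.5% to 0% (k = 3), and from about 15% to 0% (k = 4).

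**Step 7: set against the precision already planned.** A design effect of 2 with 18 per kebele implies an ICC of (2 − 1)/(18 − 1) = 0.059. At 15.5% uptake the between-kebele SD is √(0.059 × 0.155 × 0.845) = 8.8 points. The SD of the arm difference from all kebele-level causes is 8.8 × √(2/8) = 4.4 points.

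The overall standard error is √[2 × (0.155 × 0.845 + 0.355 × 0.645)/144] = 7.07 points. Replacing the alphabetical component with the distance-ordered one gives:

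- 20 points: √(50.0 − 12.2 + 3.4) ≈ 6.4, about 9% smaller.
- 10 points: √(50.0 − 3.1 + 0.9) ≈ 6.9, about 2% smaller.

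**The case against.** The strongest reply is that the plan contains no error of validity. Each kebele has the same chance of either arm, the six permutations are equally likely, and alphabetical order introduces no bias. A reader might infer from the blocking rule that the randomisation is flawed or that the treatment effect will be biased. The documents do not support that: this is chance imbalance, and a correct cluster-level variance reflects it.

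The imbalance is also not extra noise on top of the plan. Even the 3.5-point SD under the steepest gradient lies within the 4.4 points that the design effect already allows for.

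A reader might also infer that access certainly varies widely. The protocol does not say so. The districts are chosen because screening is available there, the invitation is to a facility nearby, and kebeles far from one another need not differ in distance to a facility. The 20-point gradient is as large as the whole target effect and exceeds the assumed control uptake; at 10 points the chance of a 5-point gap is only 0.3%, even with alphabetical blocks.

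District stratification does balance district-level factors, and the comparability sentence opens with a softer claim before it ends in a firm one. Covariates for the uptake model may be fixed in a document not shown.

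All of this stands, and it limits the point to efficiency and wording. It does not defend the ordering itself: the blocks do no work beyond equal numbers, and a more useful order costs almost nothing.

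**Conclusion.** The point holds as a worthwhile improvement to a valid design. Alphabetical blocks add no balance beyond the district stratum and the 4:4 split. Ordering by access would cut the variance of the access imbalance by 72% if kebeles are evenly spaced in access. The gain in overall standard error is about 2% to 9% for assumed gradients of 10 to 20 points, together with arms that look more alike on a factor readers will ask about.

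These sizes rest on the assumed gradient, the even spacing, and the inference that access differs between kebeles; the protocol quantifies none of them. It would go too far to say that the scheme balances nothing, that the comparison is biased, or that a spurious effect is likely. The closing claim that comparability will be ensured is too strong for eight kebeles per arm with district as the only balancing factor.

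**What to change.** Before allocation, order the eight kebeles in each district by travel distance or time to the nearest facility offering cervical screening. Form the two blocks of four from that order (four nearest, four farthest) and draw the permutations from sealed lots as planned. Reflect the blocks or the distance in the uptake model, so that the analysis benefits from the balance.

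If allocation has already taken place, prespecify kebele distance as a single covariate in the Generalized Estimating Equation model for uptake, with a small-sample correction for 16 clusters.

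In either case, replace the closing claim in the Randomization section with a statement that the scheme balances district and the blocking factor only.

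Cost: the distances must be ranked before allocation, for which rank order is enough, and a kebele-level covariate uses one degree of freedom out of few. No additional women, visits or staff are needed, and the total of 288 stays as it is.

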### Sampling procedure

Sixteen clusters (kebeles) will be selected from the two study districts where cervical cancer screening service is currently available. Sixteen clusters are taken based on the recommendation that taking fewer subjects from many clusters give better representation of the sample than taking many participants from fewer clusters. The clusters will be randomly assigned in to intervention and control groups. Census will be carried out in the selected Kebeles to identify women who are eligible for screening and create sampling frame. Then, simple random sampling technique will be performed to select study participants from each arm. We will select equal number of participants from each cluster which consequently leads to selection of 18 participants per cluster. The same sample of participants will be used at the end of the intervention phase, six months later, to measure the outcome variables (Fig 2).

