### Data collection methods

Data will be collected using structured questionnaire designed for meeting the specific research purpose. The tool has been developed based on the research objectives from relevant literature sources. The data collection instrument will be pretested to check for its clarity, logical sequence, cultural appropriateness etc. and appropriate modification will be made accordingly. Participants will be interviewed to complete baseline survey after randomization of the clusters and end line survey at the end of the intervention period in six months. Participants will be measured for socio-demographic characteristics, knowledge, attitudes, and cervical cancer screening uptake.

Data will be collected through face to face interview technique using paper printed data collection tools contacting each woman at her residential home. Data collectors will go to each selected woman’s home physically by carrying all the data collection tools and communicate verbally with the local language to get the required information. Two different teams will be assigned for the intervention administration and data collection for the purpose of masking the intervention from data collectors. Both the baseline and end line data will be collected by the same individuals to ease the data gathering process.

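### Eligible women are listed, sampled, consented and interviewed at baseline after kebeles are allocated, with listing by the workers who deliver the intervention and nothing that conceals the arm from them

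*Protocol article*

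**What the plan says.** **Order of steps.** The Recruitment of participants section starts with allocation: "We will randomly assign the selected clusters in to intervention and control groups using block randomization technique". It then says "We will conduct a census and/or use health post records to identify all the eligible women", after which the frame is built and "we will employ simple random sampling technique to select study participants from each cluster for each arm". The Sampling procedure section has the same order, with allocation followed by "Census will be carried out in the selected Kebeles to identify women who are eligible for screening and create sampling frame". Consent is obtained immediately before the baseline interview (Recruitment of participants). The Data collection methods section is explicit on timing: "Participants will be interviewed to complete baseline survey after randomization of the clusters".

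**Who does what.** Under Randomization, "Health extension workers will carry out identification of eligible participants", and the same sentence gives them the administration of the intervention. Implementation of the intervention confirms that the workers of the intervention kebeles are trained to deliver it. At recruitment, "Selected women at each arm will be reached by health extension workers and the data collectors at their home". The person who takes consent is not named.

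**Masking.** Data collection methods says "Two different teams will be assigned for the intervention administration and data collection for the purpose of masking the intervention from data collectors". Randomization says that assessors will be blind to the status of the cluster, and that coded arms and clusters mask the statistician. The Abstract says that blinding is not possible.

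**The concern.** Randomising kebeles makes the kebeles comparable. It makes the women comparable only if those studied in each kebele are determined without regard to the arm. Here the list is compiled and consent is sought after allocation, and the people who compile the list have a role in one arm that they lack in the other. If women who are hard to reach or uninterested are under-listed, or refuse more often, in intervention kebeles only, the intervention arm starts with women more inclined to be screened. The uptake difference then contains a component that is not an effect of the intervention.

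The planned analysis cannot remove this. Intention to treat keeps enrolled women in their arm but cannot restore women who were never listed or who declined. Subtracting baseline uptake does not help either. Women screened in the last 5 years are ineligible, and the baseline proportion covers the same 5 years, so as written it should be close to zero in both arms whoever is enrolled.

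The same staffing bears on measurement. The primary outcome is partly interview-based, and the same data collectors return at end line. If they learn the arm while visiting homes with the health extension workers, the end-line interview is no longer masked.

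**Working it through.** **1. Which steps follow allocation, and is each protected?**

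| Step | After allocation? | Protected from knowledge of the arm? |
|---|---|---|
| Listing eligible women | Yes, by order of description in two sections | No: done by health extension workers; no concealment stated |
| Drawing 18 women per kebele | Yes, by order of description | Yes, within the list: simple random sampling |
| Consent | Yes, because it directly precedes baseline | Not stated; health extension workers are among those who reach the women |
| Baseline interview | Yes, explicit | Partly: a separate data-collection team, but joint visits |

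Two of the four steps, listing and consent, have no stated protection. The listing source is also unsettled: Recruitment of participants allows a census, health post records or both, while Sampling procedure says census.

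**2. The plan's sample size, to fix the scale.** Inputs from the Sample size section: 15.5% against 35.5%, one-sided 5%, power 80%, design effect 2, allowance 5%. The two-proportion formula with continuity correction gives 68 per arm.
- 68 × 2 arms = 136
- 136 × 2 = 272
- 272 / 0.95 = 286.3, rounded up to 287
- with equal kebeles, 16 × 18 = 288

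The stated 288 is reproduced and is not in dispute.

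**3. Size of a possible bias (assumed values).** The documents give no figure for selective listing or refusal. Assume no true effect, 15.5% uptake in both arms, and a fraction f of women who would never be screened lost only in intervention kebeles. Observed uptake there is 0.155 / (1 − f).

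| f | Observed uptake | Spurious gain | Share of the 20-point effect |
|---|---|---|---|
| 5% | 0.155 / 0.95 = 16.3% | 0.8 points | 4% |
| 20% | 0.155 / 0.80 = 19.4% | 3.9 points | 19% |
| 30% | 0.155 / 0.70 = 22.1% | 6.6 points | 33% |

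**4. What that does to the test.** Effective women per arm are 144 × 0.95 / 2 = 68.4. For a one-sided 5% normal test of two proportions, the rejection probability is Φ[(d − 1.645 × SE0) / SE1]. Here d is the spurious gain, SE0 the pooled and SE1 the unpooled standard error. For f = 20%, d = 0.0388, SE0 = 0.0649 and SE1 = 0.0648. This gives Φ(−1.05), about 15%. In the same way f = 5% gives about 6% and f = 30% about 26%, where the nominal rate is 5%.

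**5. Masking statements side by side.** The Abstract says blinding is not possible. Randomization says assessors are blind. Data collection methods says separate teams mask the data collectors. Recruitment of participants sends the future delivery staff to the homes together with the data collectors. The first statement conflicts with the next two, and the fourth weakens them.

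**The case against.** The strongest reply is that health extension workers do not choose participants. The frame is meant to hold every eligible woman, and a fixed number is drawn at random from each kebele. That safeguard is real and closes the most obvious route. It leaves omission from the list and differential refusal open.

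A second reply is that only the baseline interview is explicitly placed after randomization. The position of the census is inferred from sentence order, and no text says when the workers learn their arm. This also stands. But two sections give the same order, and the codes described under Randomization serve to mask the statistician, not the workers.

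Several stronger readings are tempting and are not supported:
- **That health extension workers interview the women or take consent.** Interviewing belongs to a separate team, and the consent-taker is unnamed.
- **That the joint visits contradict the two-team arrangement or break the masking.** They take place in both arms, and health extension workers visit homes as usual care, so their presence does not by itself reveal the arm. The visits create a risk of disclosure. Their presence at end line is not stated, and masking of the statistician is unaffected.
- **That the listing source differs by arm.** Nothing says so; the two sections only need reconciling.
- **That intervention workers would pass over women without a husband.** The husband takes part in the second contact and eligibility does not require one, but the motive is inferred.
- **That losses of 20% to 30% are to be expected.** They have no source. The only loss figure in the protocol is 5% for incomplete data and non-response, which does not cover omissions from the list.

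**Conclusion.** The point holds as a design weakness that opens a route to bias; it does not show that bias will occur. Consent and baseline follow allocation, and listing and sampling do so by the described order. Listing rests with the delivery staff, who also help to reach the women, and no concealment from them is stated. The size of any bias is unknown. The range of 0.8 to 6.6 points, or 4% to 33% of the planned effect, rests on one-sided loss of women with zero uptake; the upper figures are a severe case. The masking promised for data collectors is undermined rather than broken, and the three statements on blinding must be reconciled. Because the analysis cannot undo selection at enrolment, the sequence should be changed before enrolment.

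**What to change.** - Use a single listing source, the census named under Sampling procedure, in all 16 kebeles, and remove the and/or option for health post records.
- Draw the 18 women per kebele and complete consent and baseline everywhere before the lots are drawn or the allocation is revealed to the health extension workers.
- Have data collectors interview without delivery staff present, and state who takes consent.
- Report listed, approached and consenting women by arm and by kebele, so that differential listing or refusal can be seen.
- Make the Abstract, Randomization and Data collection methods agree on who is masked.

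The cost is that allocation is drawn a few weeks later. The steps are already planned, no extra staff are needed, and sample size and power do not change. No partner criterion is needed: it would narrow the target population, and it is unnecessary for this bias once listing precedes allocation.
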